##### Blood pressure, pulse wave and pulse wave velocity assessments

The brachial blood pressure will be measured with an automatic sphygmomanometer system (SphygmoCor Xcel, AtCor Medical, Sydney, Australia). A conventional brachial cuff will be inflated around the upper arm to measure brachial systolic and diastolic blood pressures which are calculated using the oscillometric technique. Brachial blood pressure and pulse waves are used to derive central aortic hemodynamic measures by applying proprietary digital signal processing and a validated mathematical transfer function [43–45]. Finally, we will obtain aortic blood pressure, the augmentation index (AIx), augmented pressure, forward wave pressure, and backward wave pressure [44, 46].

Central arterial stiffness will be determined by calculating the carotid-femoral pulse wave velocity (PWV), which is a well-established marker of aortic stiffness [47]. To calculate the PWV, applanation tonometry technique will be used to obtain carotid pulse waves, while simultaneously femoral pulse waves will be obtained from the femoral artery by a cuff placed around the upper thigh. PWV will be calculated using the ratio between the corrected carotid to femoral distance and the foot-to-foot transit time of the pressure wave from the carotid to the femoral sites. Carotid to femoral artery distance will be measured from (A) the carotid site of measurement to the suprasternal notch; (B) from the suprasternal notch to the proximal edge of the thigh cuff; and (C) from the femoral artery below the inguinal ligament to the proximal edge of the thigh cuff. Distances A and C will be subtracted from distance B and used in the calculation of PWV [43].

##### Balance assessments

The static balance will be assessed with a pressure platform (Podoprint Balance Platform, Namrol, Barcelona, Spain). All participants will perform a double leg stance with eyes open and closed. Participants will be instructed to stand erect on the platform without shoes, motionless and with their arms by their sides. Heels will be separated by 3 cm and toes forming a 30° angle. The software requires each participant to maintain this position for 52-s [26]. Three trials (3 trials with open eyes and 3 trials with closed eyes) will be performed. The total travel distance, radial area, mean mediolateral and mean anteroposterior displacements of the center of pressure will be measured at a frequency of 100 Hz using manufacturer’s specific software (PodoPrint v2.6, Namrol, Barcelona, Spain).

Static balance on a single leg will be assessed by the single leg stand test. Participants will be requested to stand without shoes and with their hands on the hips on a single leg, with the non-supporting foot placed against the inside knee. The time performing the static balance with a maximum of 30-s will be recorded. Three trials will be performed on each leg, and the best trial will be recorded. The reliability of this test was assessed in a previous study [48].

##### Functional tests

The timed up and go test will be used to assess the dynamic balance and gait speed. The test consists of rising from an armless chair with a seat height of ≈46 cm without using the arms, walking 9-mts away from the chair and going back to the chair sitting again. The time to complete the test will be recorded. The best trial out of three opportunities will be used in data analyses. Reliability of this test in people with ID was previously assessed by Blomqvist et al. (2012).

The 6-min walking test (6MWT) will be used to assess mobility and submaximal exercise performance. Participants will walk at a self-paced velocity for 6-min in a 30 m unobstructed indoor corridor. They will be asked to walk up and down, without running or jogging, as fast as they can and as far as possible within 6-min. The covered distance will be measured to the closest 0.5 m. Reliability and validity of the test were obtained for adults and seniors with ID in a previous study [49].

##### Hand-grip isometric test

Maximal isometric handgrip strength will be assessed by using a digital hand-grip dynamometer (TKK 5401, Takei Scientific Instrument Co., Ltd., Tokyo, Japan).

Participants will be instructed to seat comfortably on an armless chair. The participant will be seated with the trunk upright, elbow flexed at 90°, forearm and wrist in a neutral position and not touching the trunk. Three maximal voluntary contractions of 3–5-s will be performed with both the left and right hand, alternating hands and ensuring a recovery of 1-min between repetitions to avoid muscle fatigue. The best of the three trials of each extremity will be recorded to the nearest 0.1 kg.

After a further 3-min recovery period, we will assess the ability to maintain the maximal isometric hand-grip strength. Seated on an armless chair, participants will be asked to maintain an isometric hand-grip contraction for 10-s with each hand. Peak, maximum and average isometric strengths will be recorded to the nearest 0.1 kg with an electronic hand-grip dynamometer (Powerlab4/20THandgrip, ADInstruments, Bella Vista NSW, Australia).

##### Lower limbs isometric strength assessment

Maximal isometric strength of knee extensor and flexor muscles will be assessed with the participant seated on a knee flexion/extension machine (Salter® M-126, Barcelona, Spain) with hips and knees flexed at 90°. A strength sensor, connected to a computer with specific software for data analyses (Chronojump v.1.9.0, Barcelona, Spain), will be attached to the knee flexion/extension machine to test lower limbs isometric strength of each participant (Fig. 5). The test will consist of 3 maximal voluntary contractions (3 for extension and 3 for flexion) of 3–5-s each with 1-min rest between contractions. First, we will test the extensor muscles of the knee with the dominant leg, then the non-dominant leg and finally both legs simultaneously (total of 9 repetitions). Next, the same procedure will be followed for the knee flexor muscles. The best score of each trial will be recorded.

**Fig. 5 Fig5:**
[figure not shown]
Assessment of the maximal isometric knee extension and flexion

##### Lower limbs muscle endurance

Muscle endurance of the lower limbs will be assessed by using the 30-s chair stand test [50]. Participants will be asked to sit down and stand upright (full stance) as often as possible during 30-s without using their hands with arms folded across the chest. Three trials will be performed with a recovery of 3-min between trials. The maximum number of repetitions achieved during one trial will be recorded. The test presents good reliability in seniors (ICC = .98) [50].

##### Flexibility measurements

Flexibility will be assessed by using the chair sit-and-reach test (CSRT) and the back scratch test (BST) [50]. In the CSRT, which assess the flexibility of the hamstrings, the participant sits on a chair with one leg extended and the other leg flexed. The person is instructed to bend forward with the arms extended to touch the toes of the extended leg and maintain the position for 2–5 s. If participants do not reach the 0-point (end of the shoe), negative values will be recorded; otherwise, positive values will be recorded if they reach behind the 0-point. The best of three trials will be recorded to the nearest cm. The reliability of the test for older adults was good (ICC = .92 and .97) [51].

Shoulder flexibility will be assessed by the BST in the upright position. The extremity to be valued is above the shoulder on the same side, elbow pointing upward, the palm facing inwards and downwards and fingers extended. The other arm is placed behind the back, palm facing outward and fingers extended up the middle of the back. The distance (cm) between extended middle fingers of both hands will be assessed. The distance that is missing to join the extended middle fingers is classified as negative distance and the overlap of these, is a positive distance. Three trials will be performed by either side, recording the best of them. The reliability of the test for older adults is good (ICC = .97) [52].

##### Physical activity and sedentary behaviors assessment

To assess the PA and sedentary level of the volunteers we will use GT3X ActiGraph accelerometers (ActiGraphTM, Fort Walton Beach, FL, USA; Firmware 1.9.2) and data will be downloaded with the ActiLife 6 Software v.6.13.4.

Participants and parent(s)/legal guardian(s) will receive face-to-face instructions on how to wear the accelerometer (correct positioning and orientation) during all waking hours, as well as its placement and wear time. We will reinforce these instructions by giving an information sheet to each participant and parent(s)/legal guardian(s), along with pictures showing correct positioning of the device. The accelerometers will be fitted to the participants’ right hip and will be collected after eight days. The devices will not be worn during water-based activities.

Outcome variables will be total PA (counts/min), steps per day (steps/day), and time spent (min/day) in sedentary (0 to 99 cpm), light PA (100 to 2019 cpm) and moderate-to-vigorous PA (≥ 2020 cpm). We will replicate the intensity cutoff points from the National Health and Nutritional Examination Survey (NHANES) for adults over 18 yrs. [53]. Non-wearing time will be defined as a period of 60 consecutive minutes of zero counts with an allowance for up to 2-min of counts between 1 and 100 [54].

To have valid data, participants will have to wear the accelerometer during waking hours for ≥10 h/day [53, 55] for ≥4 (week and/or weekend) days [56, 57].

##### Quality of life assessment

Quality of life will be assessed by using the Spanish version of the Personal Outcomes Scale (POS) [58, 59]. The validity and reliability of this test in Spanish people with ID was assessed by Carbó-Carreté et al. (2015).

Personal outcomes are generally defined as valued personal experiences and circumstances that follow as a result of some activity, intervention or service. The POS measures the QoL outcomes based on eight dimensions which are arranged into three higher-order factors [60, 61]: *independence*, which encompasses personal development and self-determination; *social participation*, composed of interpersonal relations, social inclusion, and rights; and *well-being*, which includes emotional well-being, physical well-being, and material well-being. The POS aims to assess QoL in people with ID based in the above-mentioned domains and is divided into three information sources:
Self-report: assessment of subjective perspective of QoL with individual participants answering on his/her own.Report by the professional: assessment of the individual’s experiences and circumstances from the view of direct care staff or a service technician.Family report: the indicators are scored by a family member’s perspective.

Each of the eight core QoL domains has 6 items, which means that a total of 48 items are answered, using the following calculation: (3) = always, (2) = sometimes, and (1) = rarely or never. Scoring ranges from 48 to 144 for each information source, with higher scores representing better QoL.

##### Emotional and cognitive function assessments

Emotional and cognitive assessment will be performed by using the Human Figure Drawing Test (HFD test) [62]. This is a graphic non-verbal projective test that allows knowing emotions, body self-perception of body scheme, self-esteem, anxiety and aggressiveness, between others [62–64].

The HFD test has been applied in persons with ID, including Down syndrome, and other populations, and has been considered a useful instrument [63, 65–67].

After giving a blank DIN-4 paper and HB2 pencil to the participants while they are at the exercise intervention facility, the researcher will provide the following verbal instructions: “Draw a person, their full body, the best you can”. The participants will have a maximum of 15 min to perform the drawing and they will not be able to erase any part of the drawing to make corrections. The cognitive function analyses will be performed with the drawing from the HFD test by applying the Draw a Person Intellectual Ability Test for Children, Adolescents and Adults (DAP-IQ test) [68]. The DAP-IQ test evaluation system is based on 23 quantitative indicators of the drawing [68].

For the emotional analysis, we will use the Home-Tree-Person (HTP) test [69]. The HTP test implements a qualitative analysis of the characteristics, size and perspective of the drawing produced with the HFD test [69].

### Occurrence of adverse events

Participants may experience some unlikely risks or undesirable effects during the assessment of the outcome variables and PA programs. They may suffer some discomfort, fatigue or muscle soreness. These discomforts and muscle soreness are typical in sedentary people who start a PA program, but after 2 or 3 sessions these discomforts tend to disappear.

In the event that any participant suffers any discomfort, pain or problems during the evaluations or during the study, he/she will have the possibility to discuss about it with the Principal Investigator or the project coordinator the same day. In case the participant might need more counseling, an opportunity will be arranged to further discuss about the possible cause of discomfort with the Principal Investigator or the supervisor. If the participant agrees, the participant’s general practitioner will be informed so that he/she can follow up in case of injury or illness.

All adverse events as well as serious adverse events will be carefully monitored and we will record the day and time of the occurrence. The Principal Investigator and local IRB will be informed about any adverse event.

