### Participants

To be part of this study, all participants should fulfill the following inclusion criteria: a) ≥ 40-year-old and ≤ 75-year-old; b) diagnosed with mild to moderate ID; c) able to participate in activities in groups of 10 people; d) able to follow an exercise program on cycle ergometer; e) able to wear an accelerometer; f) able to walk independently; g) able to understand and perform all the fitness assessments; h) have medical clearance to perform exercise; and i) the participant and his/her parent(s)/legal guardian(s) should be willing to provide written consent.

Exclusion criteria will be: a) participants diagnosed with severe or profound ID; b) atlantoaxial instability; c) inability to walk unaided and unassisted; d) contraindications to exercise; e) use of medications that may influence the participants’ response to exercise; f) inability to communicate in Spanish/Catalan; g) unable to provide written informed consent; and h) parent(s)/legal guardian(s) not willing to provide written informed consent.

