#### Control group

The participants of the CG will continue with their activities of daily living while receiving the usual care from their centers, which exclude exercise. Participants from the CG will receive Polar M200 HR monitors (Polar Electro OY, Finland) that will be used to control changes on their activities of daily living.

They will be visited be the researchers 2 to 3 times a week, during the 6 months of the intervention program. During these visits, the researchers will interview the participants to verify that their daily routines have not been modified. Given the benefits of exercise training and for ethical reasons, participants who completed the 12 months in the CG will receive SIT program for 6 months.

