An increasing number of studies have reported positive effects of different exercise programs on vascular function and structure in adults without disabilities [82–84]. On the other hand, 12 weeks of CAEP reduced arterial stiffness in young adults with ID [85]. Nevertheless, modalities of exercise training such as short intermittent-bouts of high-intensity exercise, should be further explored in adults without intellectual disabilities and, even more, in adults and seniors with ID. In addition, the present study will help us to understand whether the mode of exercise training (CAEP vs SIT) plays a role in central and peripheral cardiovascular improvements. On top of that, this trial will complement available descriptive data on arterial stiffness and will give information regarding the changes on aortic stiffness and hemodynamics at mid-term (6 months) and whether these changes are maintained after the end of the programs (12 months).

In the present trial we will also evaluate qualitative parameters such as QoL and cognitive and emotional aspects of participants with ID. We consider that QoL in seniors with ID is a very important parameter, which is influenced by PA and sports practice [86, 87]. Beside the positive effects on QoL, PA may also improve cognitive and emotional aspects in people with ID, as previous studies have shown after implementing dance programs [64, 88].

It was reported that high-intensity exercise of short duration appears to produce lower effort perception values than continuous or longer duration exercise [89], and it seems that enjoyment of and preferences for interval exercise are equal or greater than for continuous exercise [90]. Moreover, shorter high-intensity protocols may have the potential to reduce some of the barriers to exercise and promote positive psychological responses [91, 92]. A study found that high-intensity interval exercise is as feasible as continuous moderate intensity exercise in adults with severe mental illness [93]. Thus, SIT programs may be a feasible and effective strategy to increase exercise adherence in seniors with ID.

The findings of this trial will help the development of new exercise interventions, prescription and strategies designed to promote physiological and psychological positive changes in seniors with ID. We believe that prescribing SIT programs aimed at reducing health problems, sedentarism and increasing PA levels is a meaningful research effort that is of great value.

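### The adverse-event section describes a participant-initiated route and no scheduled enquiry common to the three arms, so event counts may be incomplete and not comparable between exercise and control

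*Protocol article*

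**What the plan says.** The adverse-event text is in the protocol article, Methods, Occurrence of adverse events. If a participant has discomfort, pain or a problem during the evaluations or the study, "he/she will have the possibility to discuss about it with the Principal Investigator or the project coordinator the same day". Further counselling can be arranged, and the general practitioner is informed if the participant agrees. The section then states: "All adverse events as well as serious adverse events will be carefully monitored and we will record the day and time of the occurrence". It closes: "The Principal Investigator and local IRB will be informed about any adverse event". It does not say who asks about events, whom they ask, how often, or whether this is the same in every arm.

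Four other sections bear on the point:

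- **Participants:** those enrolled are "diagnosed with mild to moderate ID".
- **Study intervention:** both exercise arms have three 90-minute sessions a week for 24 weeks, 72 in all, with two trainers for ten participants.
- **Control group:** at the control visits, "the researchers will interview the participants to verify that their daily routines have not been modified". No other purpose is given. This section puts the visits at 2 to 3 a week, whereas Study design puts them at once a week.
- **Quality of life assessment:** the scale draws on the participant, the family and a member of staff ("Report by the professional: assessment of the individual’s experiences").

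**The concern.** The arms differ in how an event could come to notice. In the exercise arms, trainers watch participants during exertion and could see a problem that nobody reports. In the control arm, the stated reason for contact is to confirm that habits have not changed. The one concrete reporting step in either setting depends on the participant coming forward, in a population that the Background section describes as needing specific support.

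Two consequences are possible. Events may be missed in any arm because the participant does not raise them and no second informant is asked. Events may also be picked up more readily under supervision than at a control visit, so that a difference in counts partly reflects observation. At stake is the safety description of a programme that the Discussion presents as not previously designed for seniors with ID. Events that nobody asked about at the time are hard to recover later, so the method should be settled in advance.

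**Working it through.** The document states no adverse-event rate, count or safety power, so there is no figure to reproduce. The check sets the passages side by side, counts scheduled contacts, and then shows how unequal detection would act under assumed values.

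**1. Means of detection as described**

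| | Exercise arms | Control arm |
|---|---|---|
| Participant may raise a problem the same day | yes | yes |
| Supervised exertion with trainers present | yes, two per ten participants | no |
| Stated purpose of contact | training | verify unchanged routines |
| Scheduled event question described | no | no |
| Carer or staff informant for events described | no | no |

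**2. Scheduled contacts over the 24 intervention weeks** (contacts = weeks × contacts per week)

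- Exercise: 24 × 3 = 72 sessions, which is 72 × 1.5 h = 108 h of observation.
- Control, per Study design: 24 × 1 = 24 visits.
- Control, per Control group: 24 × 2 = 48 to 24 × 3 = 72 visits.
- Exercise-to-control ratio: 72/24 = 3.0 under the first statement; 72/48 = 1.5 to 72/72 = 1.0 under the second.

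Contact frequency is thus either three times higher in the exercise arms or possibly equal, depending on which section applies. Even when the numbers are equal, the content differs: supervised exercise on one side, an interview about routines on the other.

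**3. Illustration with assumed values (none is in the document)**

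Expected participants with a recorded event per arm = 30 × true risk × detection probability. Assume a true risk of 0.20 in every arm, so 30 × 0.20 = 6 participants truly have an event, and assume detection of 0.90 in exercise.

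| Assumed control detection | Exercise recorded | Control recorded | Apparent risk ratio |
|---|---|---|---|
| 0.90 | 30 × 0.20 × 0.90 = 5.4 | 5.4 | 0.90/0.90 = 1.0 |
| 0.60 | 5.4 | 30 × 0.20 × 0.60 = 3.6 | 0.90/0.60 = 1.5 |
| 0.30 | 5.4 | 30 × 0.20 × 0.30 = 1.8 | 0.90/0.30 = 3.0 |

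The true risk cancels from the ratio. At an assumed risk of 0.40 the counts double (10.8 against 10.8, 7.2 or 3.6) and the ratios stay the same. The table shows only that unequal detection alone can create an apparent difference. It does not estimate one: the ratio is one assumed number divided by another, and it is 1.0 if detection is equal.

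**4. After the intervention**

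No scheduled contact is described in any arm between W 24 and W 48, which is 24 of the 48 weeks. This applies to all arms alike, so it bears on completeness and not on the comparison between arms.

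**The case against.** The strongest reply is that the same-day sentence belongs to a paragraph on participant support, and that capture is covered by the next paragraph, which promises monitoring of all events. A journal article may also leave the event form, its fields and its intervals to a fuller protocol. Much of this stands, and it rules out several stronger readings that a reader might be tempted to make.

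- **That events are under-counted and counted unequally.** The text does not establish this. The monitoring sentence allows for capture beyond self-report, so incompleteness and imbalance are risks.
- **That control interviews ask about nothing but routines, or that day and time are all that is recorded.** The text gives a purpose for the visits and says "we will record the day and time of the occurrence"; it never says that nothing else is asked or recorded. Severity and relatedness fields are details that a full protocol may hold. Day and time can also be read against the session attendance and completion records described under Study intervention.
- **That the trial cannot support its suggestion about SIT.** The Discussion says that "SIT programs may be a feasible and effective strategy to increase exercise adherence in seniors with ID". Adherence is assessed by sessions attended and completed, and adverse events are not a listed outcome.
- **That participants with moderate ID would be missed most.** The document has no evidence on this. Entry requires the ability to understand the assessments, and inability to communicate in Spanish or Catalan is an exclusion.
- **That using three informants for quality of life concedes that self-report is unreliable.** That is a feature of the instrument. It shows only that the trial already reaches family and staff.

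The reply does not explain why the one concrete route described relies on the participant, with no carer or staff informant named, or why the two control visit frequencies differ. Nor does the monitoring sentence show that the arms are asked in the same way.

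**Conclusion.** The point holds as a risk to the safety data. Followed as written, the article gives the arms different means of detecting events, offers no common scheduled enquiry and names no second informant. Event counts may therefore be incomplete, and not comparable between the exercise arms and control. The size cannot be derived from the document. The illustrative apparent ratios of 1.0 to 3.0 rest entirely on assumed detection probabilities and should not be cited as an estimate. The direction is also not fixed: closer observation could produce an apparent excess in the exercise arms, while participants who do not speak up could hide events in any arm. The contact ratio of 3.0, or 1.5 to 1.0, follows from the document's two conflicting visit frequencies, and that conflict is an error in its own right. The primary VO2 peak analysis is unaffected. This is an inexpensive improvement to safety and comparability, and it does not threaten the trial's main conclusion.

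**What to change.** Keep the participant's same-day access to the team and add to it:

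1. One fixed adverse-event question, put to the participant and to a centre carer or guardian, at the same interval in all three arms during the intervention. Training sessions and control visits can carry it.
2. The same question at W 24 and W 48, covering the time since the last contact.
3. Events reported per participant by randomised arm.
4. Study design and Control group reconciled on how often control participants are visited, so that the interval can be made equal across arms.

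The cost is a short form and a few minutes at contacts that mostly exist already. The downside is that more minor events will be recorded, and under the present rule each of them goes to the IRB.
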